### Exceptions to the Eligibility Criteria

It must be emphasized that the Investigator should make every effort to ensure that all subjects who are offered entry into the trial have satisfied **all** of the inclusion and exclusion criteria outlined above. It is understood, however, that there may be circumstances in which a subject should not necessarily be disqualified for entry into the trial, i.e., if he/she just barely exceeds an exclusionary maximum laboratory result or is slightly less than an allotted timeframe cutoff. In those situations, the Principal Investigator should contact the Sponsor’s Medical Responsible to discuss whether or not to permit enrollment, and such dialogue should be summarized in a written memo for inclusion in the Investigator File and in the Sponsor’s Trial Master File.

### Criteria for Subject Withdrawal

Subjects will be informed that they have the right to withdraw from the trial at any time, without prejudice to their medical care, and are not obligated to state their reason(s). Any withdrawals must be fully documented in the e-CRF and source documents and should be followed-up by the Investigator.

### Withdrawal from the Trial

Subjects are free to discontinue the trial at any time without giving their reasons.

Additionally, the Investigator may withdraw a subject from study treatment at any time if considered to be in the subject’s best interest. Withdrawal from study treatment is mandatory in the following situations:

- Pregnancy [(see Section 7.9.2)](#_Pregnancy_and_In)
- Initiation of treatment with an investigational agent or a prohibited concomitant medication [(see Section 6.4.2)](#_Non-permitted_Medicines)
- Initiation of treatment with another (approved or non-approved) disease modifying therapy for MS
- Common Terminology Criteria for Adverse Events (CTCAE) grade IV lab abnormalities or grade IV ‘related’ serious adverse events [(see Appendix C)](#_Appendix_C-_Common_)
- Adverse events leading to prolonged dose reduction of more than two weeks
- Protocol violations, including non-compliance and lost to follow-up
- Intercurrent illness or significant worsening of previous illness
- Administrative reasons
- Withdrawal of the subject’s consent

In case of premature withdrawal from the study treatment, the assessments scheduled for the Week 24/Exit visit should be performed. [(see Section 7.2.2.3)](#_Week_24/Exit_Visit)

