### Primary and Secondary Endpoints

Primary Endpoint

The primary endpoints are the numbers of voxels (counted in milliliters) that change in VW-MTR value (both increase and decrease) from baseline to six-months in NABT of RRMS subjects treated with Rebif® as compared to NABT of HC.

Secondary Endpoints

The secondary MRI endpoints for RRMS subjects treated with Rebif® are:

- the number of voxels that increase in VW-MTR value at three months vs. baseline in NABT
- the increase and decrease in number of voxels from VW-MTR at three- and six-months vs. baseline in lesions
- brain volume using 3D-T1 imaging at three- and six-months vs. baseline in whole brain and GM
- the amount of iron deposition identified via SWI at three- and six-months vs. baseline in DGM, NABT and lesions
- lesion volume from T2-LV, T1-LV and T1-Gd-LV imaging at three- and six-months vs. baseline

The secondary immunology endpoints for RRMS subjects treated with Rebif® (six-months vs. baseline) are:

*Flow cytometry studies on CD4+ and CD8+ gated T-Cells:*

- intracellular IFN-gamma, IL-4, IL-17A, IL-17F, IL-21, IL-22 and IL-10 production
- nerve growth factor (NGF) and brain derived neurotropic factor (BDNF) secretion

*RT-PCR studies on:*

- Magnetic beads separated CD14+ monocytes
  - TLR3, 7 and 9;
  - cytokines IL-1α, IL-1β, IL-23p19, TGF-β, IL-12p70, IL-10, IL-27p28
  - cytokine receptors IL-1R1, IL-12Rβ, IL-23R, IL-21R, and IL-27R.
- Magnetic beads separated CD4+ and CD8+ T-cells
  - transcription factors T-bet, GATA3, ROR, IRF4 and FoxP3;
  - cytokines IFN-gamma, IL-4, IL-17A, IL-17F, IL-21, IL-22 and IL-10;
  - cytokine receptors IL-1R1, IL-23R, IL-21R, IL-12Rβ and IL-27R,
  - neurotrophic factors NGF and BDNF

Other secondary endpoints of the study examine potential associations of the effects of Rebif® in the CNS with peripheral effects on:

- number of clinical relapses
- time to first clinical relapse
- immune cell phenotype: related to CNS infiltration (Th17 cells)
- immune cell production of neurotrophic factors: related to remyelination or preservation of gray matter volume, and
- ferritin and transferrin levels: potentially associated with levels of CNS iron deposition.

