### Follow-up for Discontinued Subjects

If a subject fails to return for follow-up, attempts should be made to contact the subject to determine if the reason for not returning is an adverse event. If a subject withdraws his/her consent to continue in the trial, an attempt must be made to follow-up with the subject.

If treatment is prematurely discontinued, the primary reason for discontinuation must be recorded in the appropriate section of the e-CRF, and all efforts will be made to complete and report the observations as thoroughly as possible. If, for any reason, a subject withdraws or is withdrawn from the trial, every attempt will be made to conduct a follow-up visit with the subject (with all assessments for Week 24/Exit to be completed) [(see Section 7.2.2.3)](#_Week_12/Exit_Visit). Also, all ongoing adverse events will be followed until resolution or at least a period of four weeks ± four days from the last treatment date. After three documented attempts for the four week follow-up telephone call and contact has not been made, subject is considered lost to follow-up.

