#### Week 24/Exit Visit

**RRMS Subjects**

The following procedures and assessments will be performed at the Week 24/Exit visit or following early termination of a subject from the trial:

- Recording of adverse events and concomitant medications/procedures
- Laboratory Assessments (Chemistry, Hematology, ferritin, transferrin, CBC, LFTs, platelets, uric acid)
- A blood sample will be collected for analysis of thyroid function tests.
- Physical examination unrelated to MS, including height, weight and vital signs [(see Section 7.2.6.1)](#_Physical_Examinations)
- Neurological assessment (full exam, not including EDSS) [(see Section 7.2.6.2)](#_Neurological_Assessments)
- Blood collection for Immunological Samples
- MRI
- For female subjects of childbearing potential, a urine pregnancy test, to be performed locally at the study site
- Reason for termination (if subject terminates early)
- Drug accountability

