### Immunological Assessments

Immunological samples will be taken on Study Day 1 for RRMS and HC subjects. Immunological samples will be taken on Week 24/Exit Visit for RRMS subjects only (for specific information on samples [see section 5.1.2](#_Primary_and_Secondary)):

The preparation and handling of blood samples for immunological testing, including the collection, labeling, storage and shipment requirements will be supplied in a separate instruction manual.

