## Description of Statistical Analyses

### General Considerations

All statistical tests will be two-tailed and considered significant at an α=0.05 level of significance; all confidence intervals will be two-sided 95% confidence intervals.

Dropouts, if any, will be examined. Subjects who stop the Medicinal Product will be asked to remain in the study and will be analyzed with the intention to treat, but adding a covariate that alternative therapies have been given. Individual data will be analyzed. No imputation of missing data will be performed.

T-tests and chi-square tests for independent samples will be used for comparison of demographic and clinical characteristics between RRMS patients and HC.

VW-MTR and SWI spatial distribution analysis will be conducted directly on the images. Analysis of MRI measures may require a variance stabilizing transformation, if skewness is observed in their assessments. Each of the MRI parameters will be examined and appropriate transformations will be applied, if necessary.

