### Analysis of Secondary Endpoint(s)

Secondary endpoints will be summarized at Baseline (if available), Week 12 and Week 24/Exit, using the same descriptive statistics used to analyze the primary endpoint as described above. Testing differences between groups and across time will be analyzed similarly to the primary endpoint.

Further details will be provided in a separate Statistical Analysis Plan (SAP), which will be finalized prior to performing any analyses.

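### Early-termination assessments share the Week 24/Exit visit, so six-month secondary and immunology results can include much shorter intervals, and a true Week 24 scan is not assured for subjects who stop the drug

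*Protocol*

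**What the plan says.** **Collection.** Section 5.4.5 ties the Exit set to stopping treatment: "In case of premature withdrawal from the study treatment, the assessments scheduled for the Week 24/Exit visit should be performed". For RRMS subjects, section 7.2.2.3 uses one list for both occasions: "The following procedures and assessments will be performed at the Week 24/Exit visit or following early termination of a subject from the trial". That list includes MRI, ferritin, transferrin and immunology blood. Section 5.4.7 asks for the same set at a follow-up visit after any withdrawal, and section 5.4.9 expects prematurely discontinued subjects to have at least the Week 24/Exit visit. The schedule in Appendix A has no early-termination column, and its Week 24/Exit column is marked as six months. On immunology, section 7.2.5 says: "Immunological samples will be taken on Week 24/Exit Visit for RRMS subjects only". It is the only sample after baseline.

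**Analysis.** The primary endpoint in section 5.1.2 is change "from baseline to six-months in NABT of RRMS subjects treated with Rebif", compared with healthy controls. Section 8.4.2 summarises it at 12 and 24 weeks. The immunology endpoints in section 5.1.2 compare six months with baseline. Section 8.4.3 says: "Secondary endpoints will be summarized at Baseline (if available), Week 12 and Week 24/Exit". The primary (ITT) set in section 8.3 requires only one injection from an RRMS subject.

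**Subjects who stop the drug.** Section 8.4.1 says: "Subjects who stop the Medicinal Product will be asked to remain in the study". They are analysed by intention to treat, with a covariate for alternative therapies and no imputation. Section 7.2.3 places the closing telephone call for early withdrawals four weeks after the withdrawal date.

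**The concern.** One visit name covers two different things: an assessment about 24 weeks after baseline, and an assessment at whatever week a subject happens to leave. An analysis that follows the visit name pools them. The VW-MTR measure is derived by subtracting maps from two time points (section 7.2.6, MRI Analysis), and immune and iron markers may depend on how long treatment lasted and whether it has ended. A result labelled six months would then no longer describe six months.

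The second issue is collection. If a site treats the Exit set done at stopping as the subject's last scan, the true Week 24 scan is never acquired. No later analysis rule can recover it, and withdrawn subjects are not replaced (section 5.4.6).

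**Working it through.** The protocol gives no dropout rate or power calculation, so there is no stated figure to reproduce. The check has three parts.

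**1. Does the text place early-exit data at the six-month time point?**

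- *Immunology and other secondary endpoints:* yes, if the wording is followed. Sections 5.4.5, 5.4.7 and 7.2.2.3 put early-exit data under Week 24/Exit, and section 8.4.3 analyses that visit. For immunology no other post-baseline sample exists.
- *Primary endpoint:* not stated. Sections 5.1.2 and 8.4.2 say six months and 24 weeks, and section 7.1 allows a seven-day window around scheduled contacts. However, the only scan slot that can supply the six-month value is Week 24/Exit, and no sentence excludes an Exit scan outside the window. An exit before Week 12 also has no clear place in the period factor of section 8.4.2 (first against second three months).

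**2. Is a true Week 24 scan taken after the drug is stopped?** Section 8.4.1 implies continued follow-up. Section 5.4.5 triggers the Exit set at withdrawal from treatment, and section 7.2.3 starts the four-week clock for the closing call at early withdrawal. None says whether the subject is scanned at stopping, at Week 24, or both.

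**3. How far could intervals shrink?** Inputs: 25 RRMS subjects (section 5.1.4) and 24 weeks. The number of early exits *k* and the exit week *t* are assumptions.

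Mean interval = ((25 − k) × 24 + k × t) / 25

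Shortfall = k × (24 − t) / (25 × 24)

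| k | t = 4 | t = 8 | t = 12 | t = 16 |
| --- | --- | --- | --- | --- |
| 1 | 23.20 wk (3.3%) | 23.36 (2.7%) | 23.52 (2.0%) | 23.68 (1.3%) |
| 3 | 21.60 (10.0%) | 22.08 (8.0%) | 22.56 (6.0%) | 23.04 (4.0%) |
| 5 | 20.00 (16.7%) | 20.80 (13.3%) | 21.60 (10.0%) | 22.40 (6.7%) |

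The range is 1 × 8 / 600 = 1.3% to 5 × 20 / 600 = 16.7%. If only in-window scans counted, every interval would lie between about 23 and 25 weeks, taking the window as seven days either side (the sign is not legible in the text).

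Exposure follows from the section 6.1 titration table at three injections a week. A subject stopping after Week 4 has received 3 × (2 × 8.8 + 2 × 22) = 184.8 mcg. A completer receives 184.8 + 20 × 3 × 44 = 2,824.8 mcg. The early stopper therefore has 184.8 / 2,824.8 = 6.5% of the completer's dose, over 4/24 = one sixth of the interval.

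**The case against.** The best defence is that Week 24/Exit is only a collection label. Assigning off-schedule visits to analysis windows is normal SAP content, and section 8.4.3 defers further detail to an SAP that is not shown. The true interval is not lost either, because section 10.2 requires dated images and laboratory listings. This stands for the windowing rule taken alone. It does not answer the collection question, since an SAP cannot supply a scan that was never taken.

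It can also be said that no passage makes the Exit set at stopping replace the Week 24 visit, and that section 7.2.6 schedules a Week 24/Exit MRI for everyone. That is correct, so the fault is an ambiguity and not a proven omission.

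Three stronger readings are tempting, and the protocol does not support them:

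- *That a Week 4 scan will be analysed as the six-month primary value.* Sections 5.1.2, 7.1 and 8.4.2 point the other way, and the bar on imputation in section 8.4.1 sits badly with such a substitution.
- *That the error is one-sided, pulling RRMS values toward the controls.* Drug-related stopping is confined to RRMS subjects, but controls can also withdraw. A subject leaving because of worsening disease could show more change, not less. A pull toward the scan-rescan floor in section 3.1 assumes that change accrues steadily.
- *That early exits are distinctive for exposure below 44 mcg.* Completers also spend 4 of 24 weeks (16.7%) in titration. Exposure is wholly below 44 mcg only for stops by Week 4.

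**Conclusion.** The point holds for the secondary and immunology endpoints: as written, their six-month results can include data from much shorter intervals. Immunology is the clearest case. For the primary endpoint it is a gap in the wording only: the text indicates 24 weeks but leaves off-window Exit scans unassigned. Sections 5.4.5, 5.4.9, 7.2.3 and 8.4.1 also leave it unclear whether subjects who stop the drug have a Week 24 scan.

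The 1% to 17% fall in mean interval rests on assumed numbers and weeks of exit. It measures interval length, not bias in any endpoint, and it does not show the effect on the rank-based ANCOVA. Without a dropout rate the size and direction of bias stay open. The change is worth making before enrolment because it is cheap and the missing scans could not be recovered later.

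**What to change.** 1. Give assessments at premature withdrawal their own Early Termination label in sections 5.4.5, 5.4.7, 5.4.9 and 7.2.2.3 and in Appendix A, and record the actual study day.
2. State that only scans and samples within the Week 24 window count as six-month data, for primary and secondary endpoints alike. List the others, or use them in a sensitivity analysis that adjusts for time since baseline.
3. Reconcile sections 5.4.5, 5.4.9 and 7.2.3 with section 8.4.1, so that subjects who stop the drug but stay in the study keep the scheduled Week 24 MRI and blood draw as their six-month assessment. Safety assessments at stopping stay unchanged.

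**Cost:** a few sentences and one e-CRF visit label. The six-month sample becomes slightly smaller. Where the research scan waits until Week 24, a subject who then fails to return has no scan after stopping.

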### Definition of End of Trial

This trial will be considered as completed after:

- all enrolled subjects, who have received at least one dose of Rebif® have completed all scheduled visits (including all prematurely discontinued subjects who should undergo at least the Week 24/Exit visit and the four-week, post-treatment telephone call);
- follow-up of all subjects with ongoing adverse events at the conclusion of treatment has been addressed; [(see Section 7.9.1.6)](#_Monitoring_of_Subjects)
- all data discrepancies have been resolved;
- the database has been locked; and
- the study site has undergone a final closure visit (usually four to six weeks after the database lock).

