### Non-permitted Medicines

In line with the exclusion criteria in [(see Section 5.4.2)](#_Exclusion_Criteria), subjects may not use any investigational medications or any of the following therapies during the trial:

- Cytokine or anti-cytokine therapy
- Any interferons other than Rebif®
- Intravenous immunoglobulin (IVIg)
- Monoclonal antibodies, mitoxantrone, cytotoxic or immunosuppressive therapy including but not limited to cyclophosphamide, cyclosporin, methotrexate, azathioprine, linomide, teriflunomide, laquinimod, cladribine, total lymphoid irradiation, anti-lymphocyte monoclonal antibody treatment (e.g., natalizumab, alemtuzumab/Campath, anti-CD4)
- Chronic or monthly pulse corticosteroids
- Plasmapheresis
- Glatiramer acetate
- Telbivudine

If the administration of a non-permitted concomitant medication becomes necessary during the trial, the subject should be withdrawn from the trial. [(see Section 5.4.4)](#_Criteria_for_Subject)

Any additional concomitant therapy that becomes necessary during the trial and any change to concomitant drugs must be recorded in the corresponding section of the e-CRF, noting the name, dose, duration and indication of each drug.

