# Appendices

## Appendix A - Schedule of Assessments

| RRMS Subjects | | | | | |
| --- | --- | --- | --- | --- | --- |
| **Study Phase** | **Screening** | **Baseline** | **Treatment** | | **Telephone** |
| Visit | 1 | 2 | 3 | 4 | 5 |
| **Study Procedure** | **within 14 days** | **Study**  **Day 1** | **Week 12 (3 Mos.)** | **Week 24/Exit (6 Mos.)** | **Safety Follow-up Call** |
| Informed Consent/HIPAA/ Eligibility Criteria | X |  |  |  |  |
| Medical History/Demographics | X |  |  |  |  |
| Physical/ Neuro Exam | X1 |  | X | X |  |
| Laboratory Assessments (chem. heme, ferritin, uric acid) | X |  | X | X |  |
| Thyroid Function Tests2 | X |  |  | X |  |
| Adverse Events/ Concomitant Meds/Procedures | X | X | X | X | X |
| Pregnancy Testing (Serum) | X |  |  |  |  |
| Immunological Samples |  | X |  | X |  |
| Samples Shipment |  | X |  | X |  |
| Pregnancy Testing (Urine) |  | X |  | X |  |
| Drug Dispensing/Accountability |  | X | X | X |  |
| Injection Training |  | X |  |  |  |
| MRI |  | X | X | X |  |

1 Includes EDSS (screening visit only)

2 Thyroperoxidase Antibody test only analyzed if T3, T4 or TSH were elevated

| Healthy Controls | | | | | |
| --- | --- | --- | --- | --- | --- |
| **Study Phase** | **Screening** | **Baseline** | **Treatment** | | **Telephone** |
| Visit | 1 | 2 | 3 | 4 | 5 |
| **Study Procedure** | **within 14 days** | **Study**  **Day 1** | **Week 12 (3 Mos.)** | **Week 24/Exit (6 Mos.)** | **Safety Follow-up Call** |
| Informed Consent/HIPAA/ Eligibility Criteria | X |  |  |  |  |
| Medical History/Demographics | X |  |  |  |  |
| Adverse Events/ Concomitant Meds/Procedures | X | X | X | X | X |
| Physical/Neuro Exam | X |  | X | X |  |
| Laboratory Assessments (chem. heme, ferritin, serum pregnancy) | X |  |  |  |  |
| MRI |  | X | X | X |  |
| Immunological Samples |  | X |  |  |  |
| Pregnancy Testing (Urine) |  | X |  | X |  |
| Samples Shipment |  | X |  |  |  |

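### The protocol does not say when a subject who stops Rebif but stays in the study has the final MRI, and Section 6.4.2 removes from the trial the therapy switchers for whom Section 8.4.1 plans a covariate

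*Protocol*

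**What the plan says.** **Stopping drug.** Section 5.4.5 says: "In case of premature withdrawal from the study treatment, the assessments scheduled for the Week 24/Exit visit should be performed". It names no date and refers to Section 7.2.2.3. There, the RRMS procedures, MRI among them, "will be performed at the Week 24/Exit visit or following early termination of a subject from the trial".

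**Leaving the trial.** Section 5.4.7 treats the two events separately. When treatment ends early, the reason is recorded and observations are to be completed as fully as possible. When a subject leaves the trial, "every attempt will be made to conduct a follow-up visit with the subject (with all assessments for Week 24/Exit to be completed"). Section 5.4.9 counts the trial as complete after all scheduled visits, "including all prematurely discontinued subjects who should undergo at least the Week 24/Exit visit".

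**Analysis.** Section 8.4.1 says: "Subjects who stop the Medicinal Product will be asked to remain in the study and will be analyzed with the intention to treat". The same sentence goes on to describe how the model handles therapy switches: "but adding a covariate that alternative therapies have been given". The section rules out imputation. The primary endpoint in Section 5.1.2 is change from baseline to six months.

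**Labels.** In Appendix A the last MRI sits in a single column whose heading begins "Week 24/Exit (6 Mos". Section 8.4.3 also summarises secondary endpoints at a combined Week 24/Exit time point.

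**Switching therapy.** Section 6.4.2, whose list includes other interferons and glatiramer acetate, says: "If the administration of a non-permitted concomitant medication becomes necessary during the trial, the subject should be withdrawn from the trial". Section 5.4.5 lists the same event, and the start of another disease-modifying therapy, as reasons for withdrawal from study treatment.

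**The concern.** Stopping drug and leaving the trial are different events, and an intention-to-treat analysis depends on keeping them apart. Section 8.4.1 does so, but 5.4.5 attaches the Exit assessments to stopping drug, while the section it cites attaches an early Exit visit to leaving the trial. Two things are at stake.

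- **Timing of the last scan.** If the Exit MRI is done when drug stops, its date is set by an event rather than by the calendar. It may then be the only scan under the Week 24/Exit heading. Healthy controls take no drug, so this trigger exists on one side of the RRMS versus control comparison only.
- **Loss of scans.** If a subject who starts another therapy leaves the trial under 6.4.2, no six-month scan is scheduled. The covariate in 8.4.1 then has no six-month value to act on for that subject. Section 5.4.6 does not replace withdrawn subjects, and 8.4.1 does not impute.

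**Working it through.** The protocol gives no figure to reproduce: it states no stop rate, and Section 8.1 says the sample size has no statistical basis. The check is a comparison of the rules, followed by an illustration.

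**1. One subject through the rules.** Take an RRMS subject who stops Rebif at week 10 (a chosen example) and agrees to stay in the study.
- 5.4.5: the Exit assessments apply, at an unstated time.
- 7.2.2.3: the occasions are Week 24 or early termination from the trial. This subject has not left, so only Week 24 fits.
- 5.4.7: the visit with all Exit assessments is for subjects who leave the trial. For stopped treatment it asks only for complete observations.
- 8.4.1: the subject remains, so the Week 12 and Week 24 scans are still due.

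Three courses are open: scan at the stop, scan at Week 24, or both. Nothing says whether an early Exit scan replaces the Week 24 scan or how it is labelled.

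**2. A subject who starts glatiramer acetate.**
- 6.4.2: out of the trial.
- 5.4.5: off study treatment.
- 8.4.1: analysed by intention to treat, with a covariate for alternative therapy.

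If 6.4.2 is followed, 5.4.7 produces at most an Exit scan at the time of leaving, and the Week 24 scan is lost. The three rules cannot all be carried out.

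**3. When an Exit scan counts as off schedule.** Section 7.1 allows seven days at each scheduled contact, read here as plus or minus 7. Week 24 is day 24 × 7 = 168, so the window is day 161 to day 175. A scan before week 23 falls outside it.

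**4. Illustration only.** Inputs: 25 RRMS subjects (Section 5.1.6 aside, the number is in Section 5.1.4). Assumed: k early scans, all at week t, all used as six-month values, with change building up linearly from zero.

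- Share of the 24-week change captured = t/24: 4/24 = 17%, 12/24 = 50%, 20/24 = 83%.
- Relative fall in the RRMS mean = (k/25) × (1 − t/24).

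| k of 25 | week 4 | week 12 | week 20 |
|---|---|---|---|
| 1 (4%) | 3.3% | 2.0% | 0.7% |
| 3 (12%) | 10.0% | 6.0% | 2.0% |
| 5 (20%) | 16.7% | 10.0% | 3.3% |

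Extremes: 0.04 × 0.1667 = 0.0067 and 0.20 × 0.8333 = 0.1667.

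The Section 8.4.2 model also contrasts the first three months with the second. A week-16 Exit scan taken as the end of the second period would cover 16 − 12 = 4 of its 12 weeks.

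**5. With the timing fixed.** Drug-stoppers who stay are scanned between day 161 and day 175. If k subjects leave the trial and their Exit scans are kept apart, 25 − k have a true six-month value: 24, 22 or 20 for k = 1, 3 or 5.

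**The case against.** **5.4.5 may just be loosely worded.** Its heading concerns withdrawal from the trial, its list includes consent withdrawal and loss to follow-up, and it cites 7.2.2.3. Study treatment could be a slip for the trial. Doing the assessments at the planned Week 24 would also fit 5.4.7, 5.4.9 and 8.4.1, and 7.2.2.3 lists occasions without forbidding others. This stands as one possible reading. The text does not choose it, and a site has to act on the text.

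**Misfiling is not shown.** A reader might infer that early scans will enter the primary analysis as six-month values. The protocol does not support that. Section 5.1.2 fixes six months, 8.4.2 summarises the primary endpoint at 12 and 24 weeks, and 10.2 requires scan images to carry the procedure date and the file to hold the date of withdrawal from trial or drug. An early scan can be recognised, and an analysis plan can assign it correctly. It cannot supply a Week 24 scan that was never taken, and that part of the point survives.

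**The percentages are not evidence.** This is right. Section 3.1 reports scan-rescan volumes of 1.44 mL increasing and 1.48 mL decreasing with no true change, so the measure does not start at zero. With such a floor and linear growth above it, an early scan captures more than t/24, and the table overstates the fall. The between-group test is on ranks, so a percentage of the mean does not carry over to it. A scan prompted by disease activity could move the value the other way.

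**Relapse as forced withdrawal.** A reader might also infer that the illness item in 5.4.5 makes a relapse end treatment. The protocol as a whole speaks against it: relapses are endpoints in 5.1.2, have their own recording rule under 7.9.1, and may be treated with corticosteroids under 6.4.1.

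**Conclusion.** The conflict is real and rests on the text alone. The protocol leaves open when a drug-stopper who remains in the study is scanned, so an early Exit scan could stand in for the six-month scan, through a trigger that exists in the RRMS group only. Sections 6.4.2, 5.4.5 and 8.4.1 also disagree on whether a therapy switcher is still in the trial, and following 6.4.2 loses six-month scans that the intention-to-treat analysis needs.

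Size and direction of any bias are unknown. Each RRMS subject is 1/25 = 4% of the group. The 0.7% to 16.7% range depends wholly on assumed stop counts, assumed stop weeks and linear accrual, and is not an estimate. The documents do not show that the primary result would be wrong. They show that the data needed for it may not be collected on time. When a scan is taken is a matter for the protocol, so the point is more than a detail left to the analysis plan.

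**What to change.** **Section 5.4.5.** State that subjects who stop Rebif but remain in the study have MRI on the scheduled Week 12 and Week 24 dates. State that an early Exit MRI is done only for subjects leaving the trial, and is recorded as an early Exit scan with its study week, not as Week 24.

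**Section 6.4.2.** Change it so that starting another MS therapy or other non-permitted drug ends Rebif but not follow-up. Leave the investigator free to end participation for safety, for example after a pregnancy or when the subject takes an investigational agent. Dropping the covariate from 8.4.1 would also make the sections agree, but it would accept the loss of the scans.

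**Cost.** A short change of wording in 5.4.5 and one sentence in 6.4.2. Stopped subjects return for visits already in the schedule. Subjects who leave the trial have no six-month value, because 8.4.1 allows no imputation.
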